#### **Maintenance of randomisation codes and procedures for breaking code**

Only the trial team and the data manager at the Nottingham CTU will be aware of the allocation to intervention or control group. Since the intervention is clothing, no special arrangements are necessary for breaking of the randomisation code.

#### **TRIAL MANAGEMENT**

The trial is funded by the NHS Health Technology Assessment Programme. It is sponsored by the University of Nottingham, and will be managed and co-ordinated from the Centre of Evidence Based Dermatology in Nottingham and the Nottingham Clinical Trials Unit.

The Trial Steering Committee (TSC) will meet at least once a year and will provide overall supervision of the trial on behalf of the trial sponsor.

The Trial Management Group (TMG) will meet more frequently and will be responsible for the day-to-day management of the trial. Members of the TMG will report to the TSC at their meetings.

Due to the low risk of the clothing, no data monitoring committee will be required.

The Chief Investigator has overall responsibility for the study and shall oversee all study management.

The data custodian will be the Chief Investigator.

## **DURATION OF THE TRIAL / STUDY AND PARTICIPANT INVOLVEMENT**

The overall duration of the study is anticipated to be approximately 36 months. It is planned that recruitment will take up to 18 months. Target recruitment for the pilot phase of the trial is 75 participants enrolled over the first 6 months of recruitment.

Each participant will participate in the trial for 8 months (treatment period) and her/his participation will commence upon signing the consent form. Participants will be randomised to intervention or control groups for the first 6 months. Participation in the RCT will end after 6 months, at which point participants in the control group (standard care) will be given the therapeutic clothing and will be followed up until 8 months post randomisation. Participants allocated to the intervention group will continue with their randomised intervention until the garments are no longer usable. Further supplies of clothing will not be given to these patients during the follow-up period from 6 to 8 months post-randomisation.

Participation in the qualitative component will be a maximum of 2.5 additional hours after completing their final 8 month contact.

### **End of the Trial**

The end of the RCT will be receipt of the last questionnaire of the last participant.

The end of the qualitative study will occur when the final focus groups and interviews are completed for the sub-set of patients who have volunteered to participate in the qualitative component and the cohort of commissioners and clinicians have been interviewed..

## **SELECTION AND WITHDRAWAL OF PARTICIPANTS**

### **Recruitment**

Recruitment into this trial will be based in six secondary care hospitals (with further contingency centres as required). GP practices and other local hospitals in the surrounding area will be approached to act as Patient Identification Centres (PICS).

Potential participants will also be identified through direct local advertising (including but not limited to e-mail distribution lists, radio and TV interviews, websites and articles). If other potential sources for recruitment become apparent during the trial, these will also be included. A dedicated website will be available for the purpose of this trial.

If identified through secondary or primary care the initial approach will be from a member of the patient's usual care team (which may include the investigator), and information about the trial will be on display in the relevant clinical areas. The initial approach may be made by invitation letter or in person at a clinic.

The investigator or their nominee, e.g. from the research team, will inform the participant and their parent/legal guardian of all aspects pertaining to participation in the study.

If needed, the usual hospital interpreter and translator services will be available to assist with discussion of the trial, the participant information sheets, and consent forms, but the consent forms and information sheets will not be available printed in other languages.

It will be explained to the potential participant and their parent/legal guardian that entry into the trial is entirely voluntary and that their treatment and care will not be affected by their decision. It will also be explained that they can withdraw at any time.

### **Eligibility criteria**

#### **Inclusion criteria**

- Children aged 1 to 15 years at baseline.
- Diagnosis of moderate or severe eczema (atopic dermatitis). Presence of eczema will be confirmed using the UK Diagnostic Criteria for Atopic Eczema ([Williams, Burney et al. 1994](#)) and eczema severity judged using the Nottingham Eczema Severity Scale (NESS) ([Emerson 2000](#))
- Resident within travelling distance of a recruiting centre.
- Children with at least one patch of eczema on the trunk or limbs
- Parent/legal guardian able to give informed consent

#### **Exclusion criteria**

- Children who have taken systemic medication (including light therapy) or oral steroids for eczema within the previous three months.
- Children who have started a new treatment regimen within the last month.
- Children who have used wet/dry wraps  $\geq 5$  times in the last month.
- Children who are currently using silk clothing for their eczema and are unwilling to stop using the clothing during the trial.
- Children who are currently taking part in another clinical trial.
- Children who have expressed a wish not to take part in the trial.

#### **Additional guidance on eligibility criteria**

*‘Children who have started a new treatment regimen within the last month’* are excluded from taking part in the trial. This should be interpreted as a new treatment regimen for eczema, or if they have started or are currently using any treatment that may affect eczema

A change in treatment regimen for eczema would include a change in strength of topical corticosteroids or addition of calcineurin inhibitors, and therefore the child would be excluded. However, changes to the same strength of steroid, and changes to emollients are acceptable. Changes in diet to help control eczema are also acceptable, as well as the use of antibiotics, in the previous 3 months, for an infection due to the child's eczema.

Any new or existing treatment for other conditions that require anti-inflammatory medications e.g. oral steroids for asthma, arthritis or inflammatory bowel disease, would also fall under this exclusion criteria and therefore the child would not be eligible to take part. However, steroid inhalers for asthma do NOT fall under this exclusion criteria.

The use of oral antihistamines, NSAIDs and steroid inhalers within the past month are permitted. If any of the following treatments have been used within the last month, for any condition, the child would be excluded: methotrexate, ciclosporin, prednisolone, azathioprine, light therapy, mycophenolate mofetil.

Only one child will be enrolled per family. The choice as to which child becomes involved will be made by the parents and children involved, taking into account the eligibility criteria above.

Included in the 8 month letter to parents and children, parents/guardians will be sent an invite to the qualitative component of the study, as well as parent and age-appropriate child information sheets. Patients and their families may choose to contact the Qualitative Lead to express interest in the interviews/focus groups.

Children and Parents/ guardians will be aware that not choosing to take part in the qualitative interviews/ focus groups will in no way effect their participation in the RCT or their future care.

Prescribers and commissioner will be identified via existing dermatology networks at the beginning of the study and brief telephone interviews arranged.

### **Eligibility Criteria for the Optional Qualitative Component:**

#### **Inclusion criteria**

##### **Children**

- Participants in the main CLOTHES trial.
- Parent / guardian able to give informed consent.
- Child able to give assent.

##### **Parent / guardians**

- Parent / guardian of child in the main CLOTHES trial
- Able to give informed consent.

##### **Prescribers / commissioners**

- Active involvement in prescribing or commissioning eczema treatments, including but not limited to the provision of silk garments for childhood eczema.

#### **Exclusion criteria**

##### **Children**

- Unwilling to take part
- Unable to converse in English language

##### **Parent / guardians**

- Unwilling to take part
- Unable to converse in English language

##### **Prescribers / commissioners**

Unwilling to take part

### **Expected duration of participation**

Study participants will be enrolled in the study for 8 months.

Study participants (See Qualitative Component Research Methods, page 24 for maximum numbers) who opt to do the additional qualitative interview/focus group will extend their participation for another 2.5 hours beyond the 8 months of the RCT and RCT follow-up.

### **Removal of participants from therapy or assessments**

Participants (child or parent/ legal guardian) may be withdrawn from the trial at any time. They will be made aware (through the participant information sheets) that withdrawing from the trial will not affect their future care, but that the data already collected cannot be erased and will still be used in the final analysis. The primary reasons for discontinuation/withdrawal will be recorded.

Participants who withdraw after randomisation will not be replaced.

## **Informed consent**

### **RCT**

All parents/legal guardians will provide written informed consent for their child to take part in the trial. The Informed Consent Form will be signed and dated by the parent/legal guardian before they enter the trial. For children wishing to do so, assent will be given on the same form, but this will not be mandatory. In the event of any conflict between the parent's and child's wishes, the child WILL NOT enter the study. The Investigator will explain the details of the trial and provide age appropriate Participant Information Sheets, ensuring that the participant and/or parent/legal guardian has sufficient time to consider participating or not. The Investigator will answer any questions that the child and/or parent/legal guardian has concerning study participation.

Separate informed consent will be obtained for the provision of a saliva sample (for genetic testing), and parents / legal guardians will be offered the possibility of opting out of this part of the study if they wish. No samples will be taken until informed consent has been gained. In line with current guidance patients will not receive their filaggrin test results ([Fabsitz, McGuire et al. 2010](#))

Informed consent will be collected from each parent/legal guardian before they undergo any interventions (including physical examination) related to the study. One copy of this will be kept by the parent/legal guardian, one will be kept by the Investigator, and a third will be retained in the child's notes.

Should there be any subsequent amendment to the final protocol that might substantially affect a participant's participation in the trial, continuing consent will be obtained using an amended Consent form, which will be signed by the parent/legal guardian.

### **Qualitative Interview/ Focus Group**

The Investigator facilitating the focus group or interview will obtain consent from each participant at the onset of the interview/ focus group. Parents/guardians and children will have been provided with detailed, age appropriate Participant Information Sheets in the 8 month RCT study mailing, and will be given them again at the onset of the interview/focus group. Prior to the interview or focus group, they will have the opportunity to ask questions about the qualitative study. The Investigator will explain the details of the qualitative component and answer any questions that the participant has.

Parent / guardians will provide written consent prior to participation of themselves and their child. Children will have an opportunity to sign assent forms if appropriate for their age and ability to understand the study. In the event of any conflict between the parent / guardian and child the child will not enter the study.

Consent will be obtained on one occasion only. One copy will be kept by the participant and one will be kept by the Investigator,

Verbal consent will be taken, and noted, at the beginning of interviews with prescribers/commissioners.

## TRIAL INTERVENTION AND REGIMEN

### Interventions:

#### **Silk clothing:**

The medical device under investigation is a knitted, sericin-free silk therapeutic garment with a CE mark for use in eczema. Sericin is a protein that coats the outside of silk fibres and has the potential to cause allergic reactions. Medical grade silk (such as silk used for stitches during operations), has the sericin removed for this reason.

The specific products being used are Dreamskin™ and Dermalilk™. The silk clothing will be worn at night, and when possible during the day. Participants will receive three sets of garments (long-sleeved vest and leggings, or body suits and leggings depending on the age of the child). This will give sufficient garments to allow for washing between uses. Washing instructions will be provided in line with manufacturers recommendations. Adherence in wearing the garments will be collected using sticker/tick charts as an aide memoir and weekly questionnaires.

The clothing will have product labels removed and be supplied using trial-specific packaging prior to distribution from the co-ordinating centre. Clothing will be replaced as required during the six-month RCT (e.g. because they are worn out or because the child has grown). Once the randomised part of the trial is complete at six months, garments will NOT be replaced.

Participants will be asked about their use of clothing and willingness of GPs to prescribe them at 8 months. It will be explained to participants at this stage that it is not possible for the trial team to recommend use of the garments, or to insist that their GPs prescribe them.

Participants allocated to the therapeutic clothing will continue to use their standard eczema care (including emollients, topical corticosteroids and topical calcineurin inhibitors).

#### **Standard care:**

All participants (active and control groups) will continue with their standard eczema care in line with NICE guidance ([NICE December 2007](#)). No efforts will be made to intervene or change a child's standard eczema care unless the research nurse thinks that the skin may be infected. If research nurses suspect infection they will recommend that the patients contact their normal medical team (GP, Nurse, dermatologist) as appropriate.

Standard advice about what clothing to use for a child with eczema will be provided (avoid wool, and wear cool loose clothing – especially cotton and linen), but specific products will not be recommended.

If a child is currently using "specialist" cotton clothing (e.g. special sleep suits with built-in mittens), the use of these garments will be recorded, but will not be grounds for exclusion. However, participants in the control group will be asked to refrain from using prescription clothing (including silk clothing and synthetic garments used for wet wrapping) during the trial.

**Table 2 - Study Assessments**

= RCT

= observational period

| Outcomes collected                                                                                | 0 months          | 2 months  | 4 months  | 6 months  | 8 months |
|---------------------------------------------------------------------------------------------------|-------------------|-----------|-----------|-----------|----------|
| Informed consent for main study                                                                   | √                 |           |           |           |          |
| Informed consent for genetic study (optional)                                                     | √                 |           |           |           |          |
| Eligibility checks                                                                                | √                 |           |           |           |          |
| Eczema severity (NESS)                                                                            | √                 |           |           |           |          |
| Supply garments                                                                                   | √
intervention |           |           | √ control |          |
| Demographics                                                                                      | √                 |           |           |           |          |
| Collect saliva sample (Optional)                                                                  | √                 |           |           |           |          |
| Issue diary                                                                                       | √                 | √         | √         | √         |          |
| EASI & TIS                                                                                        | √                 | √         | √         | √         |          |
| Investigator and Patient Global Assessment (IGA and PGA)                                          | √                 | √         | √         | √         |          |
| Topical treatment usage                                                                           | √                 | √         |           | √         |          |
| Medication for skin infection                                                                     | √                 | √         | √         | √         |          |
| Use of wet and dry wraps                                                                          | √                 | √         | √         | √         |          |
| On-line questionnaire (weekly) including POEM, topical treatment use and use of wet and dry wraps |                   | √         | √         | √         |          |
| Final on-line questionnaire                                                                       |                   |           |           |           | √        |
| DFI                                                                                               | √                 |           |           | √         |          |
| EQ-5D-3L of parent                                                                                | √                 |           |           | √         |          |
| Child utility scales (ADQoL, CHU-9D)                                                              | √                 |           |           | √         |          |
| Number of infections                                                                              | √                 | √         | √         | √         |          |
| Serious adverse events                                                                            |                   | √         | √         | √         |          |
| NHS and family resource use                                                                       | √                 | √ & Diary | √ & Diary | √ & Diary | √        |
| Adherence                                                                                         |                   | Ques      | Ques      | Ques      | Ques     |
| Durability of clothing                                                                            |                   |           |           | √         | √        |
| Acceptability (parent & child)                                                                    |                   |           |           | √         | √        |
| Replace garments if required (intervention group only)                                            |                   | √         | √         |           |          |

NESS = Nottingham Eczema Severity Scale; TIS = Three Item Severity scale; EASI – Eczema Area and Severity Index; POEM = Patient Oriented Eczema Measure; DFI = Dermatitis Family Impact questionnaire; EQ-5D-3L – EuroQol Five Dimension, Three Levels questionnaire; CHU-9D – The Child Health Utility 9 dimensions; Ques = Weekly on-line/postal questionnaire

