### **Secondary endpoints**

- a) Global assessment of the eczema, assessed by research nurses (Investigator Global Assessment: IGA) and by participants (Participant Global Assessment: PGA) at baseline, 2, 4 and 6 months.

- b) Three Item Severity scale (TIS) at baseline, 2, 4 and 6 months, assessed by the research nurses and used to assess eczema severity.
- c) Use of topical treatments: use and potency of topical steroids and topical calcineurin inhibitors, use of emollients and frequency of wet / dry wrapping throughout the trial.
- d) Self reported eczema symptoms using the Patient Oriented Eczema measure (POEM)([Charman, Venn et al. 2004](#))
- e) Health Related Quality of Life at baseline and 6 months: Dermatitis Family Impact (DFI)([Lawson, Lewis-Jones et al. 1998](#)); will assess the impact of the child's health on the whole family, EQ-5D-3L will provide a utility measure for the main carer; and age-appropriate utility measures (Atopic Dermatitis Quality of life preference based index ADQoL)) will be used to provide an eczema-specific utility score([Stevens, Brazier et al. 2005](#)), and a general health utility score for the child (CHU-9D)([Stevens 2012](#))
- f) Durability of the garments, adherence and acceptability of use (as assessed by children and parents/carers).
- g) Cost-effectiveness and cost utility.

The number of children with mutations on the gene encoding for filaggrin will also be reported and used to inform a planned sub-group analysis, to test the hypothesis that children with at least one mutation on the gene encoding for filaggrin are more likely to respond favourably to the therapeutic clothing if it compensates for loss of barrier function. Specific consent for this testing will be obtained.

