## **RANDOMISATION AND BLINDING**

The randomisation schedule is based on a computer generated pseudo-random code using random permuted blocks of randomly varying size, created by the Nottingham Clinical Trials Unit (CTU) in accordance with their standard operating procedure (SOP) and held on a secure University of Nottingham server. The randomisation is stratified by recruiting hospital and by child's age - <2years; 2 to 5 years; and >5 years.

Access to the sequence will be confined to the data management team and administrators at the Nottingham CTU who will be responsible for distribution of the clothing. Investigators and Research Nurses will access the randomisation website by means of a remote, internet-based randomisation system developed and maintained by the Nottingham CTU. The sequence of treatment allocations will be concealed until interventions have all been assigned and recruitment, data collection, and all other trial-related assessments are complete.

Participants will be informed of their treatment allocation by letter from the co-ordinating centre. Those allocated to receive the therapeutic clothing will receive their first supplies at this time. Participants will be randomly allocated to one of the therapeutic clothing brands available on prescription in the UK as they enter the trial. They will not be aware of which brand of clothing they have received. Packaging, labelling and distribution of clothing will be performed by staff at the co-ordinating centre and sent to participants by post. Sizes will be determined by collection of the participant's height at randomisation

Whilst it will not be possible to blind participants to their treatment allocation, efforts will be made to minimise expectation bias by emphasising in the trial literature that the evidence supporting the use of therapeutic clothing for eczema is currently limited, and that we do not

yet know if this clothing offers any benefit over standard care. The study literature will also avoid the use of terms such as “specialist” or “therapeutic” clothing for the same reason.

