## **Data Collection Methods**

### **Face-face visits with the research nurse**

These interviews will take place at baseline (recruitment visit), 2 months, 4 months and 6 months.

The visits will include the following:

- i. check of eligibility criteria (recruitment visit only)
- ii. baseline characteristics / demographics (recruitment visit only)
- iii. collection of single saliva sample –optional (planned to be collected at the recruitment visit but can be collected at any visit according to patient preference)
- iv. examining the child's skin for disease severity and signs of infection (using the Eczema Area and Severity Index, EASI); Three Item Severity score – TIS; and Investigator Global Assessment, IGA).
- v. Patient-reported eczema severity (Patient Global Assessment, PGA) and number of skin infections treated with antibiotics or anti-viral treatments
- vi. Review of topical medication usage (prescriptions issued and changes in treatment regimen)
- vii. Review of health resource use (e.g. visits to GPs or nurses in relation to eczema treatment)
- viii. Quality of life questionnaires (at baseline and 6 months only) – dermatitis family impact questionnaire, EQ-5D, eczema utility scale and CHU-9D.

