### **Treatment diaries /memory aides**

All participants will be given an eczema diary as an aide memoir to record health resource use and a sticker chart to record progress in the trial – participants randomised to wear the clothing for the first six months will have a chart where they can record when they have worn the clothing and participants randomised to the control group will have a chart to record each week they have been in the trial.

Each week the parent / legal guardian, if they have expressed a wish to complete the questions on-line will be sent a link (via e-mail) to an on-line questionnaire. This short questionnaire will be completed by referring to the diary / wall chart, and will record how their eczema has been that week, health service resource use (including, prescriptions and health professional contacts related to eczema), days of usage of: topical steroids, emollients, topical calcineurin inhibitors and wet/dry wraps, and adherence with / the clothing (intervention group only).

Participants who do not wish to complete the questions on-line will be asked to complete a form and post it back to the Clinical Trials Unit.

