### **Sample size and justification**

Three hundred participants provides 90% power, at the 5% significance level (two-tailed) to detect a difference of around 3 points between the groups in mean EASI scores over 2, 4 and 6 months using a repeated measures analysis of covariance, assuming a SD of 13, a correlation between EASI scores at different time points of 0.6 and loss to follow up of 10%.

A 3-point improvement in EASI represents a small but still clinically meaningful difference between groups, and we are keen to ensure that the study is sufficiently powered to detect this magnitude of difference since it is unlikely that a trial like this will be done again. A small treatment response could still be worthwhile to the NHS since this non-pharmacological treatment is assumed to have no adverse effects, and because eczema affects so many people. It is also likely that a relatively small response on the objective primary outcome will be reflected in larger, more clinically meaningful treatment effects in the patient-reported outcomes.

Participants will be recruited from six recruiting centres over an 18 month recruitment period. Recruitment is expected to increase gradually over the first 6 months of the trial to allow for staggered site set-up.

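### No baseline POEM is scheduled, so this secondary endpoint cannot be adjusted for its own starting value or checked for balance on it

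*Protocol*

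**What the plan says.** The protocol's Secondary endpoints section lists, as item (d), "Self reported eczema symptoms using the Patient Oriented Eczema measure (POEM"), and gives no time points for it. Items (a), (b) and (e) of the same list each name baseline.

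In Table 2 POEM occurs only within the row "On-line questionnaire (weekly) including POEM, topical treatment use and use of wet and dry wraps". That row is ticked at 2, 4 and 6 months and its 0-month cell is empty. The other two contents of the row, topical treatment use and wraps, each also have a separate row with a 0-month tick. The rows for EASI and TIS, IGA and PGA, DFI, EQ-5D-3L, and ADQoL and CHU-9D are ticked at 0 months too.

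The section on face-to-face visits with the research nurse lists what is done at recruitment. Its patient-reported items are "Patient-reported eczema severity (Patient Global Assessment, PGA") with the number of treated infections, and "Quality of life questionnaires (at baseline and 6 months only"), which names DFI, EQ-5D, the eczema utility scale and CHU-9D. POEM is not among them.

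On timing, the section on treatment diaries says of the weekly questionnaire: "This short questionnaire will be completed by referring to the diary / wall chart". Of the chart it says "participants randomised to wear the clothing for the first six months will have a chart where they can record when they have worn the clothing", while controls get a different chart. The randomisation section says "Participants will be informed of their treatment allocation by letter from the co-ordinating centre", with the first garments sent at the same time.

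The sample size section expects the modest EASI effect to be accompanied by "larger, more clinically meaningful treatment effects in the patient-reported outcomes".

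**The concern.** A continuous symptom score measured repeatedly is normally analysed with its own pre-randomisation value as a covariate, as this protocol does for EASI. POEM has no such value. Two things are lost: the covariate likely to explain most of the between-child variation in follow-up POEM, and the chance to see whether the arms differed on POEM at the start.

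The gap lies in data collection, so the SAP cannot close it, since a score that was never taken cannot be modelled or tabulated. It matters somewhat more here because the case for a small EASI target rests partly on what the patient-reported outcomes are expected to show, and POEM is the endpoint labelled as self-reported symptoms.

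**Working it through.** **Is a baseline POEM scheduled anywhere?** Three places could schedule one.

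- Endpoint (d) gives no times.
- Table 2 has no 0-month tick for the only row that contains POEM.
- The recruitment-visit list omits POEM; its entry for baseline characteristics and demographics names no instrument.

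The end-of-trial questionnaire is at eight months. So no baseline POEM is scheduled.

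**Can the first weekly score stand in?** The weekly questionnaire is completed from a diary or chart, the chart differs by arm, and in the intervention arm the questionnaire also asks about wearing the clothing. It therefore runs after randomisation. The protocol does not date the first one against the allocation letter, so knowledge of allocation by then is a strong inference and not a stated fact. In either case the score is not scheduled before randomisation.

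**How much precision is at stake?** The protocol gives no SD, correlation, target difference or power for POEM, so there is no POEM figure to reproduce. Its EASI figure can be checked and shows how far the planning relies on a same-instrument baseline.

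- Inputs (Sample size and justification): SD 13, correlation ρ = 0.6, three follow-ups, difference 3, N = 300, loss 10%, so 270 evaluable or 135 per arm.
- Variance factor for the mean of k scores, unadjusted: v = (1 + (k − 1)ρ)/k. Adjusted for own baseline: v − ρ².
- k = 3: v = 2.2/3 = 0.733; adjusted 0.733 − 0.36 = 0.373.
- Adjusted SD = 13 × √0.373 = 7.94. This needs 148 per arm (296 in total) before loss. Power is 90.5% with 300 and 87.4% with 270, and the difference detectable with 90% power at 270 is 3.13, which fits the protocol's rounded 3 points.
- Unadjusted SD = 13 × √0.733 = 11.13. Power with 270 falls to 60.0%.

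For POEM, **assume** a constant correlation ρ between all scores, take 0.6 from EASI for want of a POEM value, and average 24 weekly scores:

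| k | ρ | Unadjusted v | v − ρ² | Ratio |
|---|---|---|---|---|
| 24 | 0.3 | 7.9/24 = 0.329 | 0.239 | 1.38 |
| 24 | 0.6 | 14.8/24 = 0.617 | 0.257 | 2.40 |
| 24 | 0.7 | 17.1/24 = 0.7125 | 0.2225 | 3.20 |
| 3 | 0.6 | 0.733 | 0.373 | 1.96 |

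A ratio of 2.40 means a confidence interval √2.40 = 1.55 times as wide without the covariate.

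**Against a proxy covariate.** Another baseline measure that correlates c with each follow-up POEM (c is an assumption) leaves v − c². With k = 24 and ρ = 0.6:

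| c | v − c² | Ratio to 0.257 |
|---|---|---|
| 0.3 | 0.527 | 2.05 |
| 0.4 | 0.457 | 1.78 |
| 0.5 | 0.367 | 1.43 |

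At c = 0.6 the proxy would do as well as POEM's own baseline, and the precision gain would vanish.

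**The case against.** The strongest case on the other side accepts the gap and disputes its weight. Most of it stands.

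- A reader might infer that POEM is the main patient-reported outcome. The protocol does not say so. POEM is one of seven unranked secondary endpoints, PGA is also patient-reported and has a baseline, and the sample size section speaks of patient-reported outcomes in general.
- A reader might infer that no baseline adjustment is possible, or that chance imbalance would be confused with effect. Neither follows. Baseline PGA, EASI, TIS and NESS are collected and can be covariates. Randomisation keeps the unadjusted comparison unbiased in expectation, and its confidence interval already allows for chance imbalance. What proxies cannot do is show balance on POEM itself.
- A reader might take the 2.4-fold figure as the cost of the omission. It compares with no adjustment at all, borrows a correlation meant for EASI at two-monthly visits, and supposes an average of weekly scores that the protocol does not specify.
- A baseline POEM would not remove open-label reporting, since every follow-up POEM still comes from an unblinded family.
- The blank cell belongs to a weekly questionnaire that has no reason to run before enrolment, and the visit list does not name every instrument: NESS, for example, is in Table 2 only. This is why the point is that no baseline POEM is scheduled. NESS, however, has its own 0-month tick, whereas POEM has none anywhere.

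**Conclusion.** The point holds as a loss of precision, and of a POEM-specific balance check, on one secondary endpoint. The primary outcome is unaffected and the POEM comparison is not biased by the omission.

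Own-baseline adjustment would cut the variance about 2.4-fold against no adjustment (1.4 to 3.2 for correlations of 0.3 to 0.7; 2.0 for three scores at 0.6). Against a proxy covariate correlating 0.5 to 0.3 with POEM, the cut is about 1.4 to 2.1-fold. These figures assume a constant correlation, an EASI value applied to POEM, and an average of 24 weekly scores. They do not show that the POEM comparison would be underpowered, because the protocol sets no target for it.

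The omission looks unintended, given that the two other contents of the same questionnaire row have their own 0-month ticks. Correcting it is a cheap improvement.

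**What to change.** Schedule POEM at the 0-month visit, completed before randomisation:

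- add a POEM row, or a separate 0-month tick for POEM, to Table 2;
- add POEM to the recruitment-visit items in the section on face-to-face visits;
- state the POEM time points in secondary endpoint (d);
- use baseline POEM as a covariate in the POEM analysis, as baseline EASI is used for the primary outcome (the model itself can be set out in the SAP).

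The first weekly score should not be used as a baseline. The cost is one short questionnaire at an existing visit and a minor amendment to Table 2 and the baseline CRF. A baseline cannot be recovered for children already randomised, so the change is best made before recruitment starts. For any child without one, baseline PGA or EASI is the available fallback covariate.
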